## Materials and methods

3

### Study design

3.1

A multi-center 3 × 3 randomized factorial, observer-blinded experimental design was conducted to evaluate the effect of gain-, loss-versus no frame message and under-, over- versus correct risk perception. This trial will be implemented on the basis of National Basic Public Health Service Program (45) and Zhejiang Province Basic Public Service standards (2021 edition). Those includes essential health services for all citizens and chronic health management for hypertensions and diabetes, such as having a free physical examination opportunity once a year, and the electronic physical examination recorded in the community health care system, so that general practitioners (GP) could provide continuous health management services. This study was approved by the Human Research Ethics Committee of the second affiliated Hospital of Zhejiang University school of Medicine (No.2023-0877). It was registered and approved by China Clinical Trials Center (ChiCTR2300076337). We followed the SPIRIT guidelines, and all participants will be followed up for 3 months (Figure 1).

**Figure 1 fig1:**
[figure not shown]
Study flow chart.

### Study setting

3.2

This study will be conducted in three communities located in Hangzhou, Zhejiang Province. The health-related cultural norms and values, as well as the availability of local resources for adopting healthier lifestyles and accessing convenient medication consultation, differ between urban and rural communities. Therefore, including urban and rural sites will enhance the generalizability of the findings and facilitate result dissemination across diverse locations. As mentioned before, these risk populations had a free physical examination once a year according to the chronic disease management standard of Zhejiang Province. Thus, biochemical indicators (total cholesterol, high density lipoprotein cholesterol, etc.) were obtained from the health examination recording, eliminating the need for additional blood samples in this study. All study sites will follow the same study procedures.

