#### Eligibility criteria

3.4.1

Inclusion criteria: Aged 20–80 years old; permanent residence; accessible for reliable CVD risk calculation indicators from health examination records (waistline, blood pressure, total cholesterol, high density lipoprotein cholesterol measured in last 6 months); a 10-year risk of absolute CVD risk (based on China-PAR model) of at least 5%; had access to a telephone to receive picture or video message from WeChat; normal visual acuity and hearing (with correction); speaking with Mandarin; be able to adhere to all study procedures.Exclusion criteria: Experienced incident CVD or stroke before; experienced severe anxiety; engagement in concurrent participation in another health research study; current or planned pregnancy during the study period; restricted physical activity due to other medical conditions; and ongoing treatment for severe disease or terminal medical condition.

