#### Primary outcomes

3.7.1

The primary outcome aims to assess two key aspects: (1) CVD prevention behaviors, encompassing healthy physical activity, a balanced diet, and adherence to preventative medication; and (2) CVD absolute risk.

Healthy physical activity will be assessed using the questionnaire of self-reported International Physical Activity Questionnaire-short version (IPAQ) (54). The responses were processed and aggregated using the IPAQ guidelines for Chinese (55). Participants who achieved a minimum of 150 min of moderate-intensity physical activities or 75 min of vigorous-intensity physical activities per week were considered to have fulfilled the criteria for adequate physical activity (56).

Healthy diet will be assessed through healthy diet score based on the updated Chinese Dietary Guideline (57). The assessment included the weekly consumption of six food groups, namely fresh fruit, fresh vegetables, whole grains, fish and other seafood (consumed more than once per week), bean and bean food (consumed at least four times per week), and red meat (consumed less than seven times per week). The response that met the established criteria received a score of 1 for each food group, and the cumulative score was calculated (with a maximum score of 6). The healthy group was defined as individuals with a total score of 4 or higher (58).

Taking preventative medication will be evaluated through medical prescription for stain/lipid lowering, anticoagulants, antihypertension, glucose-lowering medications (59), based on data obtained from the community physician health check system.

The estimation of CVD absolute risk, including both 10-year and lifetime CVD risk, will be performed using the China-PAR equation (50). Participants will be classified into three groups based on the China-PAR cut-off value specified in the Chinese guidelines (56), namely low risk (<5%), moderate risk (5–9.9%) and high risk (≥10%); for lifetime CVD risk: low risk (<32.8%), and high risk (≥32.8%).

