#### Other measurements

3.7.3

To assess the manipulation check, participants were asked to rate the extent to which they believed the video messages emphasized the advantages of engaging in CVD risk management or the disadvantages of not doing so. This rating was measured on a scale of 1 to 7, with 1 indicating a greater emphasis on the benefits, 4 indicating an equal focus on both benefits and risks, and 7 indicating a greater emphasis on the disadvantages (34). Participants will be deemed to have passed the manipulation check if they choose the item that aligns with their assigned message condition (64). The level of engagement will be evaluated based on the responses to questions following each video message, with a threshold of more than 75% of responses indicating high engagement (35). The qualitative components of risk communication experience after intervention procedure finished at 8 weeks will be evaluated using semi-structured interviews with the participants. This approach enables us to investigate participants’ experiences and delve into the social, cultural, and environmental factors that may impact their responses to the intervention. Such exploration is invaluable for interpreting quantitative findings accurately and enhancing intervention program effectiveness through iterative improvements. Details of the interview outline can be found in Supplementary Table S2. Study participants will be randomly selected at each study site among enrolled samples. The interviews will be stopped once data saturation is reached (Table 1).

**Table 1 tab1:** Research activities.

	Baseline	Post assessment	Follow-up assessment
	T0	T1	T2
Informed consent	√		
Demographic, socioeconomic assessment	√		
CVD risk factors assessment	√	√	√
10-year CVD risk calculation	√		√
Lifetime CVD risk calculation	√		√
Physical activity assessment (self-reported)	√	√	√
Healthy diet assessment (self-reported)	√	√	√
Medication prescription	√	√	√
CVD related knowledge	√	√	√
CVD risk perception	√	√	√
Health related efficacy	√	√	√
Subjective health status	√	√	√
Major adverse cardiovascular events (MACE)			√
Emotional response		√	
Manipulation check		√	
Participants engagement		√	
Interviews with participants		√	

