#### Missing data plan

3.8.2

Although we aim to retain the majority of participants, missing data is inevitable when subjects withdraw for reasons beyond our control. To avoid the missing data, the researcher will systematically examine each post-video question to identify instances where subjects have not been filled and subsequently issue reminders. Besides, we set the outcome assessments on site, and the researchers will check the questionnaire to remind participants to fill in the missing data immediately. In addition, the physical examination data will be extracted from medical recordings of the community health care system to minimize missing data. The GEE model will be employed due to its ability to generate unbiased estimates, even when missing data is present, assuming the missing is completely random. Reasons for non-adherence and non-retention will be recorded.

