However, it is important to acknowledge several limitations associated with this pilot study. First of all, the assessment of outcomes was conducted over a relatively brief period based on practical reasons, necessitating further investigation into the long-term effectiveness of the intervention. Secondly, our intervention will be implemented online through smartphone (WeChat App), potentially introducing selection bias. However, there were more than 1.3 billion WeChat active users worldwide in 2023 (76) and more than one-third of individuals regularly obtained health information by WeChat in China (77), WeChat has been increasingly used for disseminating health information. In addition, the representativeness of samples was improved in our study through enrolled participants from urban and rural areas, as well as different educational level. Third, the utilization of self-report forms to assess physical activity and diet may be susceptible to recall bias. Subsequent research will explore the adoption of accelerometers (78) or image recognition technique (79) to detect the actual status of lifestyle changing. However, we did conduct objective measurements such as blood pressure, blood glucose, total cholesterol, high-density lipoprotein, etc. at the stage of pre- and post-intervention, and calculated the 10-year risk of CVD. Comparing changes in these measures also offers a way to reflect the impact of lifestyle modifications. Finally, our study was conducted in several communities within a city in southeast China, yet the sample remains non-representative of the entire population. Given the significance of cultural nuances in health communication, further research is warranted to determine the substantial impact of message framing on the improvement of risk perception and modifiable behaviors across various regions in China.

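### The protocol contradicts itself on whether post-intervention lipids exist for CVD absolute risk, a primary outcome recalculated at T2

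*Protocol article*

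**What the plan says.** Section 3.7.1 (Primary outcomes) names two primary aspects, ending with "adherence to preventative medication; and (2) CVD absolute risk". It adds: "The estimation of CVD absolute risk, including both 10-year and lifetime CVD risk, will be performed using the China-PAR equation". In Table 1 the row "10-year CVD risk calculation" is ticked at T0 and T2 but not at T1, and the lifetime-risk row is ticked in the same way.

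On the source of the lipids, Section 3.2 (Study setting) says of the biochemical indicators that they "were obtained from the health examination recording, eliminating the need for additional blood samples in this study". On how often that record is renewed, the same section says "these risk populations had a free physical examination once a year". Section 3.4.1 (Eligibility criteria) sets how old the entry values may be: "total cholesterol, high density lipoprotein cholesterol measured in last 6 months". Section 3.8.2 (Missing data plan) again points to existing records: "the physical examination data will be extracted from medical recordings of the community health care system".

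The limitations part of the Discussion (Section 4) says something different: "we did conduct objective measurements such as blood pressure, blood glucose, total cholesterol, high-density lipoprotein, etc. at the stage of pre- and post-intervention". It presents this, together with the calculated 10-year risk, as a counterweight to self-reported activity and diet.

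**The concern.** A change in absolute risk from T0 to T2 reflects the intervention only in so far as the inputs are measured again after it. Section 3.4.1 lists four record-based indicators for the risk calculation: waistline, blood pressure, total cholesterol and HDL cholesterol. Two of the four are lipids. If the T2 calculation draws them from the same examination record as the T0 calculation, they are identical at both times, and any effect of framing that acts through lipids is removed from the outcome. A null result on this outcome would then be hard to interpret.

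The Discussion relies on re-measured lipids as objective support for the self-reported behaviours. If they were not re-measured, the lipid part of that support is absent. The document states the lipid source and then contradicts it, for a primary outcome, so this goes beyond detail that an article may leave to a fuller protocol.

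**Working it through.** The document gives no figure for when a repeat lipid value becomes available, so there is none to reproduce. The check is date arithmetic.

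**Inputs**
- Age of the lipid record at T0: 0 to 6 months (Section 3.4.1).
- Examination frequency: once a year (Sections 3.1 and 3.2).
- Intervention: 8 weeks = 56 days (Section 3.6.1).
- Follow-up: 3 months (Section 3.1). Whether it runs from T0 or from the end of the course is not stated, so both are tried.
- Recruitment: October to November 2023 (Section 3.4.3).

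**Timing of T2**
- Counted from T0: 3.0 months.
- Counted from the end of the course: 56/30.44 + 3 = 1.84 + 3 = 4.84 months.

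**Reading A: examinations 12 months apart (assumption)**

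Next examination after T0 = 12 − age of the record.

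| Age of record at T0 (months) | Next examination after T0 (months) | Gap after T2 at 3.0 | Gap after T2 at 4.84 |
|---|---|---|---|
| 0 | 12 | 9.0 | 7.16 |
| 3 | 9 | 6.0 | 4.16 |
| 6 | 6 | 3.0 | 1.16 |

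Every gap is positive, so no routine re-examination falls due by T2. Even with the oldest permitted record, the interval between examinations would have to be at most 6 + 3.0 = 9.0 months, or 6 + 4.84 = 10.84 months, for a new value to exist.

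**Reading B: one examination per calendar year, spread evenly over 2024 (both assumptions)**

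The oldest permitted record for the earliest entrant (1 October 2023) dates from about 1 April 2023, so every entry record belongs to 2023 and the next examination to 2024. The share with a new value by T2 is the share of 2024 elapsed (366 days, 3 months taken as 91 days).
- T2 at 91 days: 31 December 2023 to 29 February 2024, giving 0/366 = 0% to 59/366 = 16%.
- T2 at 56 + 91 = 147 days: 25 February to 25 April 2024, giving 55/366 = 15% to 115/366 = 31%.

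These shares count any new value, including one taken before the course ends. For a participant entering on 30 November 2023 the course ends on 25 January 2024. Examinations in the first 24 days of 2024 (24/366 = 7%) would therefore be new but not post-intervention.

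**Other inputs**

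Section 3.7.2 takes physical indicators, including blood pressure and waist circumference, from GP follow-up records. Those can change by T2. Lipids are not in that list.

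**The case against.** The strongest reply is that the document itself says lipids were measured again. The Discussion states it outright, and Table 1 ticks a general risk-factor assessment at T0, T1 and T2. The Section 3.2 sentence is in the past tense and may describe screening values only. Ruling out extra study samples does not rule out tests in routine care, and participants are recruited through chronic disease clinics. Section 3.1 describes the yearly examination as an opportunity, not a fixed 12-month cycle.

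Much of this stands. A reader might infer from Sections 3.2 and 3.4.1 that lipids cannot change by T2 and that none of the 240 participants will have a new value. The documents do not support that: it assumes that Section 3.2 overrides the Discussion and that examinations are exactly 12 months apart. A reader might also infer that the whole T2 risk is a copy of baseline, or that any effect of diet or medication is forced to zero. That does not follow either, because blood pressure and waist can still move the score. Nor is the powered comparison affected: the sample size in Section 3.4.2 rests on the lifestyle outcome.

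The reply does not remove the conflict. The Table 1 row does not mention cholesterol, no Methods section schedules a post-baseline lipid measurement, and the Discussion names no source for one. Under Reading B at least 69% (100 − 31) would still carry baseline lipids at T2, alongside fresh values in the rest.

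**Conclusion.** The point holds as an internal contradiction about an input to a primary outcome. Sections 3.2 and 3.4.1 lead to baseline lipids being reused at T2; the Discussion says lipids were measured after the intervention. Which is true cannot be settled from the document.

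If Section 3.2 governs, no participant is due a new routine value by T2 at a 12-month interval. On a calendar-year reading with evenly spread examinations, about 0–16% (T2 at 3.0 months) or 15–31% (T2 at 4.84 months) could have one. Only the part of any arm difference that acts through lipids is lost. The resulting dilution cannot be computed, because the document does not give the weights in the China-PAR equation.

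A reader might conclude that the outcome should lose its primary status now. That is premature: if the Discussion is right and its lipid values postdate the intervention, the outcome is measurable as described.

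**What to change.** 1. Reconcile Section 3.2 with the Discussion, and state the source and permitted date window of the T2 lipid values.
2. Require lipid inputs to the T2 risk to be dated after the end of the intervention, and do not count a T0 lipid value as a T2 measurement.
3. Report, by arm, how many participants have a new lipid value.
4. If post-intervention lipids will not be available, hold lipids fixed in both calculations. Describe the outcome as change in China-PAR risk through the non-lipid inputs actually re-measured, and do not present it as a full change in absolute risk. Amend the Discussion accordingly.

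The cost is a date field in the extraction form and, under item 4, a narrower claim for this outcome. No extra blood tests are needed for any of these steps.

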### Blinding

3.3

Due to the inherent characteristics of the intervention, both researchers who responsible for intervention and participants will not be blinded to the group allocations. The initial collection of baseline data commenced first, after which participants will be informed of their allocated group. Two other well-trained researchers, who were blinded to group allocation, will be responsible for data collection. The investigators responsible for implementing the intervention will not participate in the data collection process. The statistician conducting the subsequent data analysis will be blinded to the group allocation.

### Participants and recruitment

3.4

#### Eligibility criteria

3.4.1

Inclusion criteria: Aged 20–80 years old; permanent residence; accessible for reliable CVD risk calculation indicators from health examination records (waistline, blood pressure, total cholesterol, high density lipoprotein cholesterol measured in last 6 months); a 10-year risk of absolute CVD risk (based on China-PAR model) of at least 5%; had access to a telephone to receive picture or video message from WeChat; normal visual acuity and hearing (with correction); speaking with Mandarin; be able to adhere to all study procedures.Exclusion criteria: Experienced incident CVD or stroke before; experienced severe anxiety; engagement in concurrent participation in another health research study; current or planned pregnancy during the study period; restricted physical activity due to other medical conditions; and ongoing treatment for severe disease or terminal medical condition.

#### Sample size

3.4.2

Previous risk communication intervention studies were utilized to estimate the sample size. In our previous survey (46), we observed a baseline proportion of healthy lifestyle adherence at approximately 30% among participants with familiar sample characteristics. For the intervention groups, we anticipate a relative increase of at least 50% (47), with an expected difference of 25% between the gain- and loss-framed groups (39). This corresponds to an estimated effect size (W) for Chi-square of 0.20 (48), aligning closely with recommendations from prior studies (38). To achieve a power of 80%, an alpha error rate of 0.05, a standard deviation of 5%, and an estimated effect size (W) of 0.20, a total of 198 participants will be required for our primary outcome, which measures a healthier lifestyle encompassing physical activity, diet, and prevention medication at 3 months. These participants will be evenly distributed into three groups: gain-framed, loss-framed, and no-frame message interventions. However, considering the dropout rate of 20%, a sample size of 240 participants will be required.

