#### Data analysis

3.8.1

Descriptive statistical analysis will be conducted for all measurements. The distributions of categorical baseline variables will be compared using χ^2^ test among the three intervention groups. The difference in continuous variables will be analyzed using either one-way analysis of variance (ANOVA) or a non-parametric rank-sum test. The differential changes in the primary (i.e., healthy behaviors) and secondary (i.e., risk perception) outcomes at T1 and T2, relative to T0, across the three groups will be assessed using generalized estimating equations (GEE) models. GEE methods were applied to estimate model parameters using a binomial distribution for the variance function, a logit link function, and accounting for clustering via an assumed exchangeable working correlation structure (65). The outcomes will be used as dependent variables (one for each model) and, as independent variables, the intervention arms (no-framed, gain-framed, loss-framed message), the factors time (T0, T1, T2), the covariates (risk perception categories) and their corresponding interaction term. The other potential confounders (i.e., variables with baseline imbalances, study sites) will be added as independent variables to adjust GEE model. An exchangeable working correlation structure will be assumed in order to assess the association between factors and outcomes. The statistical significance of each parameter in the model will be analyzed using a Wald test. To account for the potential occurrence of type 1 errors, a Bonferroni correction will be implemented for all GEE models, with a *p*-value threshold of less than 0.003 indicating statistically significant differences (66). The final model’s results will be presented as estimated odds ratio (*OR*) and 95% confidence interval (*CI*) for each significant prognostic variable. We will also conduct the sensitivity analysis to assess the non-response mechanism (67) and an attrition analysis (68) to identify the differential dropout rates and dropout by group interaction on sociodemographic and pretest variables that may pose a threat the equity of the findings (69). Subgroup analysis was performed for cases that did not pass the manipulation check. The principle of “intention to treat (ITT)” will be applied in conducting all primary and secondary outcome analyses. Moreover, the patterns of missingness would be recorded across variables and time points to provide insight into non-random missingness. Statistical significance will be determined by results with *p* < 0.05 in two-sided tests. The analysis will be carried out using SPSS software for MAC (version 26.0) and R software (version 4.3.1).

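### One effect size (W = 0.20) and one power (80%) are attached to several stated effects with different W values, so the 80% does not carry over to the separate-arm comparisons

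*Protocol article*

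**What the plan says.** Section 3.4.2 (Sample size) takes a baseline rate of healthy lifestyle adherence of about 30% from the investigators' own survey. For the framed arms it states: "we anticipate a relative increase of at least 50% (47), with an expected difference of 25% between the gain- and loss-framed groups". The next sentence reads "This corresponds to an estimated effect size (W) for Chi-square of 0.20" and adds that this value agrees with earlier studies. The calculation then uses 80% power, "an alpha error rate of 0.05, a standard deviation of 5%, and an estimated effect size (W) of 0.20", and arrives at 198 participants divided equally over three arms, raised to 240 for dropout.

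The paragraph does not say whether the 25% is absolute or relative, which contrast W describes, or how many degrees of freedom the test has. Section 2 (Objective) lists the effect of message framing on prevention behaviours as the first specific objective. Section 3.6.1 labels the no-frame arm as control. Section 3.8.1 (Data analysis) enters the three arms as separate levels in GEE models and uses two-sided tests.

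**The concern.** W for a chi-square test is fixed by the arm rates and the allocation. Once rates are given, W can be calculated for each contrast, and a single value can serve several contrasts only if they happen to share it. Here they do not, yet one W and one power are given for the whole set.

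The stake is how a null result will be read. If one framed arm does not differ significantly from no-frame, a reader who has seen 80% power will tend to conclude that framing does not work. Whether that is fair depends on the power of that particular comparison at the effect the plan anticipates. The same holds for gain against loss, where the answer turns on the unstated meaning of the 25%.

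**Working it through.** **Inputs (section 3.4.2).** No-frame rate 30%. Minimum framed rate 30% × 1.5 = 45%. Gain–loss difference 25%: absolute gives 45% v 70%, relative gives 45% v 45% × 1.25 = 56.25%. Placing the lower framed arm at the 45% minimum is my assumption. Alpha 0.05, two-sided (section 3.8.1). Evaluable N = 198, or 66 per arm.

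**Reproducing the plan's N.** With 1 df, 80% power needs a noncentrality of (1.960 + 0.842)² ≈ 7.85. N = 7.85 / 0.20² = 196.2, so 197, or 198 as a multiple of three. The step from W to N therefore reproduces with 1 df. With 2 df (three arms, binary outcome), W = 0.20 needs 241, and 198 gives 71%.

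**From rates to W.** W = √[Σ wᵢ(pᵢ − p̄)² / (p̄(1 − p̄))], where wᵢ is the share of participants in arm i and p̄ the weighted mean rate. For two equal arms this is (difference/2) / √(p̄(1 − p̄)).

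- 30 v 45: 0.075 / √(0.375 × 0.625) = 0.155
- 45 v 70: 0.125 / √(0.575 × 0.425) = 0.253
- 45 v 56.25: 0.05625 / √(0.50625 × 0.49375) = 0.113
- Framed arms pooled, 25% relative: mean framed rate (45 + 56.25)/2 = 50.625%, weights 1/3 and 2/3, p̄ = 0.4375. W = 0.20625 × √(2/9) / √(0.4375 × 0.5625) = 0.196

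**Power** (noncentral chi-square, noncentrality N·W²):

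| Contrast | Rates (%) | df | N | W | Power |
|---|---|---|---|---|---|
| One framed arm at minimum v no-frame | 30 v 45 | 1 | 132 | 0.155 | 43% |
| Other framed arm v no-frame, 25% relative | 30 v 56.25 | 1 | 132 | 0.265 | 86% |
| Gain v loss, 25% absolute | 45 v 70 | 1 | 132 | 0.253 | 83% |
| Gain v loss, 25% relative | 45 v 56.25 | 1 | 132 | 0.113 | 25% |
| Three arms, 25% absolute | 30/45/70 | 2 | 198 | 0.330 | 99% |
| Three arms, 25% relative | 30/45/56.25 | 2 | 198 | 0.217 | 79% |
| Framed pooled v no-frame, 25% relative | 30 v 50.6 | 1 | 198 | 0.196 | 79% |

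Only the last row rounds to 0.20, and it is also a 1-df test, the setting in which 198 reproduces.

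**Sensitivity of the 43%.** The pooled-variance z test gives 42.8%. Power is 41.7% with 64 per arm (240 less 20%) and 50% with all 80 per arm analysed. For 80% power at 30 v 45, 163 per arm would be needed.

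**Detectable rate.** With 66 per arm, a framed rate of 54% against 30% gives about 80% power (80.5% by the z test, 79.8% by chi-square).

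**The 5% standard deviation.** It does not enter a chi-square calculation on W. Nor is it the standard deviation of a binary outcome, which at 30% is √(0.3 × 0.7) = 0.46.

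**The case against.** The strongest reply is that 0.20 can be recovered. The plan has just used a relative increase, so reading the 25% as relative is natural. Pooling the framed arms against no-frame then gives W = 0.196, 1 df and 79% power at 198, close to everything printed. This stands. A reader might infer that W = 0.20 cannot be derived from the stated rates; the document does not support that. What the reply does not supply is any sign that this pooled contrast was intended: the paragraph does not name it, and the models in section 3.8.1 keep the three arms separate. On this same reading, gain against loss has 25% power.

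A second reply is that the plan never ties its 80% to one framed arm at 45%, and that its own gain–loss difference rules out both framed arms being at 45%. That is correct. If one is at 45%, the other is at 56.25% or 70%, with power against no-frame of 86% or more. So 43% belongs to the weaker framed arm only, and it would be wrong to say the trial has 43% power instead of 80%.

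Third, if the 25% is absolute, 0.20 is smaller than the W for gain against loss and for the three-arm test, so it is conservative there. This also stands, and a general charge of too small a sample would not be supported.

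Finally, this is called a pilot, and the analysis is a repeated-measures GEE. The first does not remove a formal power claim that readers will use. The second is a genuine limit on the figures above.

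**Conclusion.** The point holds as a mismatch between one stated power and several stated effects. The printed W and 80% fit, approximately, one pooled 1-df contrast that the plan does not name. They do not describe the separate-arm comparisons, whose power runs both below and above 80%: about 43% for a framed arm at the 45% minimum against no-frame, and about 83% or 25% for gain against loss depending on whether the 25% is absolute or relative.

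The assumptions are 66 analysed per arm, two-sided alpha 0.05, the lower framed arm at 45%, and a single-timepoint comparison of two proportions. The figures are not the power of the planned GEE, which uses repeated measurements and, under section 3.8.1, a stricter Bonferroni threshold. The evidence supports neither an impossible W nor a trial that is underpowered throughout. The correction is worth making because the 80% is a figure readers will rely on and restating it is cheap.

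**What to change.** Keep N and rewrite the paragraph in section 3.4.2:

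- State the assumed rate in each arm, and whether the 25% is absolute or relative.
- Name the contrast to which W = 0.20 and 80% power apply.
- Give W and power for each framed arm against no-frame (at 30% v 45%: 0.155, about 43% with 66 per arm) and for gain against loss (0.253 and about 83% if absolute; 0.113 and about 25% if relative).
- State the framed rate detectable against 30% with 80% power, about 54%.
- Delete the 5% standard deviation.
- State that a non-significant result for a single framed arm against no-frame does not exclude the anticipated minimum effect of 15 percentage points (45% − 30%).

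The cost is rewording, with no added participants and no change to procedures. The downside is that some of the stated power figures become less favourable.

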## Objective

2

This pilot study aims to clarify the optimal risk communication strategy by examining the compatibility between message framing (gain-framed, loss-framed, or no-framed) and risk perception subgroups (under-perceived vs. over-perceived vs. correct-perceived CVD risk), using a multi-center randomized controlled trial design in Zhejiang province, China. The specific objectives are as follows:

To evaluate the effect of message framing on CVD prevention behaviors among individuals with moderate and high CVD risk.To design a series of CVD risk communication messages based on message framing, then to implement the intervention program among individuals with different risk perception subgroups in the communities.To determine the optimal risk communication message for CVD risk populations with risk perception categories to achieve better CVD prevention behavior change, continuum maintenance, and risk reduction.

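### The total of 198 is a two-group (1-df) chi-square answer; at the stated W = 0.20 the three-arm test needs 241, and 240 enrolled with 20% dropout leaves 192 (about 70% power)

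*Protocol article*

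**What the plan says.** All the sizing is in section 3.4.2 of the protocol article. It starts from about 30% healthy-lifestyle adherence at baseline. It expects a relative rise of at least 50% in the intervention groups and a 25% difference between the gain and loss arms, and does not say whether that 25% is absolute or relative. It then says: "This corresponds to an estimated effect size (W) for Chi-square of 0.20". The design inputs are given as: "To achieve a power of 80%, an alpha error rate of 0.05, a standard deviation of 5%, and an estimated effect size (W) of 0.20". The result is that "a total of 198 participants will be required for our primary outcome".

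The next sentence makes clear that 198 is the total for the whole trial: "These participants will be evenly distributed into three groups: gain-framed, loss-framed, and no-frame message interventions". The last step is the allowance for loss: "considering the dropout rate of 20%, a sample size of 240 participants will be required". No degrees of freedom are stated.

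Section 3.8.1 analyses the outcomes by GEE. It sets a Bonferroni threshold of p < 0.003 for those models and also says: "Statistical significance will be determined by results with *p* < 0.05 in two-sided tests".

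**The concern.** W, alpha, power and the number of arms determine N for a chi-square test once the degrees of freedom are known. Three arms by a yes/no outcome is a 3 × 2 table, which has 2 degrees of freedom. The printed total looks too small for that test, and the step from 198 to 240 looks like multiplication by 1.2 rather than division by 0.8. The rates in the prose also do not obviously lead to W = 0.20, and a standard deviation has no place in a chi-square calculation.

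What is at stake is the meaning of a null result. A reader who takes the section at face value would assume a 20% type II risk for the three-arm comparison. At the section's own W, the risk is about 30%.

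**Working it through.** **Inputs (section 3.4.2):** W = 0.20, alpha 0.05, power 80%, three equal arms, stated total 198, dropout 20%, enrolled 240.

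**Method.** The power of a chi-square test is P(χ²(df, λ) > c). Here c is the 5% critical value of the central chi-square and λ = N × W² is the noncentrality. The required N is λ for 80% power divided by W² = 0.04.

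**1. Reproducing the plan's figure.** With df = 1, N = 196.2, so 197. Rounded up to three equal arms this is 3 × 66 = 198. The power at 198 is 80.4%. The printed total is therefore the 1-df answer.

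**2. The three-arm test.** With df = (3 − 1) × (2 − 1) = 2, N = 240.9, so 241.

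| Evaluable N | Power, 1 df | Power, 2 df |
|---|---|---|
| 192 | 79.1% | 69.9% |
| 198 | 80.4% | 71.3% |
| 241 | 87.4% | 80.0% |

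**3. Dropout.**
- Plan's apparent step: 198 × 1.2 = 237.6, taken up to 240.
- Correct step: 198 / (1 − 0.20) = 247.5, so 248.
- Evaluable from 240: 240 × 0.80 = 192.
- Loss that 240 can bear and still keep 198: 1 − 198/240 = 17.5%.

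Taken alone (1 df), this moves power only from 80.4% to 79.1%. With 2 df, 192 evaluable gives 69.9%. The W detectable with 80% power at 192 and 2 df is √(240.9 × 0.04 / 192) = 0.224.

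**4. Do the prose rates give W = 0.20?** For equal arms, W² = mean of (pᵢ − p̄)² divided by p̄(1 − p̄). I assume that the no-frame arm stays at 30%, that one framed arm reaches 30% × 1.5 = 45%, and that the other framed arm is 25% higher.

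- *25% absolute* (30%, 45%, 70%): p̄ = 0.4833; mean squared deviation = 0.0817/3 = 0.0272; W = √(0.0272/0.2497) = 0.33. Power at 192, 2 df: 98.9%.
- *25% relative* (30%, 45%, 56.25%): p̄ = 0.4375; mean squared deviation = 0.0347/3 = 0.0116; W = √(0.0116/0.2461) = 0.22. Power at 192, 2 df: 77.2%.

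Neither gives 0.20. The standard deviation of 5% enters none of these formulas.

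**5. The other alpha.** The same 2-df test at W = 0.20 with 192 evaluable has about 32% power at the p < 0.003 threshold of section 3.8.1.

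**The case against.** The strongest reply is that the shortfall depends on W = 0.20, and the section's own rates point to larger effects. At 192 evaluable, the 2-df power is 99% or 77% on the two readings above, both better than 70%. This stands as a limit on the claim. A reader might infer that the trial is underpowered whatever the effect. The document does not support that; it shows only that 80% is not reproduced at the W it states.

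It can also be said that 198 does come out of a 2-df calculation for rates of 30%, 45% and 20% (W = 0.22). That match needs a framed arm below the 30% starting rate, although the section expects a rise in the intervention groups, and it needs a W other than the one printed. Nor does a pairwise reading rescue the figure, since 198 is given as the total for three arms.

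Two further inferences are tempting and should not be drawn. One is to apply W = 0.20 to gain versus loss and report a power for that pair. The section gives that contrast its own difference. With 128 evaluable in two arms, power is about 82% if the 25% is absolute (45% v 70%) and about 25% if it is relative (45% v 56.25%), so no single figure follows. The other is to attach a power to the frame-by-perception interaction. The third objective in section 2, "To determine the optimal risk communication message for CVD risk populations with risk perception categories", depends on it, but section 3.4.2 gives no interaction effect size and claims no power for it, so there is no stated figure to contradict.

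Finally, the study calls itself a pilot, and its analysis is a GEE over three visits to which people lost late may still contribute. Both are true. Neither changes the fact that the section makes an explicit 80% claim and justifies it by a chi-square calculation alone.

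**Conclusion.** The concern holds for the stated calculation. At W = 0.20 and alpha 0.05, the total of 198 belongs to a 1-df test. The three-arm 2-df test needs 241 evaluable and has 71% power at 198, or 70% at the 192 who remain from 240 after 20% loss. The degrees of freedom account for most of the gap; the dropout slip is minor by itself. Separately, the printed rates do not reproduce W = 0.20 on either reading of the 25%, so the section is internally inconsistent about the effect it was sized for.

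The conclusion rests on a binary primary outcome, equal arms, the printed W and alpha, and a chi-square test. It does not give the power of the planned GEE models.

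**What to change.** Rewrite section 3.4.2; no extra enrolment is needed.

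- Name the test, its degrees of freedom and its alpha.
- Give the three assumed arm rates, say whether the 25% is absolute or relative, and show the W that they produce.
- Delete the standard deviation.
- Restate power for 192 evaluable of 240 enrolled. If W = 0.20 is kept, for example: *For a 2-df chi-square test at alpha 0.05 and W = 0.20, power is about 70% (80% at W = 0.224). This is not the power at the p < 0.003 threshold of section 3.8.1, which is about 32% for the same test.*
- State that no power is claimed for gain versus loss, or for the interaction of message frame with risk perception, unless an effect size for that contrast is given.

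The cost is text only. At the stated W, the power claim falls from 80% to about 70%. If other rates are adopted, the figure must be recomputed from their W.
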